#### **2.4.2 Control group**

Participants in the control group will perform the same intervention as the experimental group, but will not receive the physical activity monitor (Smartwatch Mi Band 7®).

## **2.5 Measurement of outcomes**

The measurement of primary and secondary outcomes will be carried out in NEUROLAB. Measurements will be carried out at the initial assessment (week 0), immediately after the end of the intervention program (week 12) and one month after the end of the intervention program (week 16). In the initial assessment (week 0), clinical and demographic data will be collected from all individuals for the purpose of verifying the eligibility criteria, identification and characterization of the sample. For this, a previously developed evaluation form will be used (APPENDIX 2). In weeks 12 and 16, a previously developed reassessment form similar to the evaluation form will be used, in addition to the addition of an assessment of the participant's satisfaction with the intervention carried out (APPENDIX 3). This collection will be carried out by a previously trained examiner, blinded to group allocation. All participants will be instructed not to comment on information about the training received.

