### **2.3 Randomization and concealed allocation**

Participants will be allocated into two groups (experimental and control). The allocation sequence will be generated by a website ([www.randomization.com](http://www.randomization.com)). A research assistant, who will not be involved in recruitment, will perform the randomization and place the sequence in opaque, numbered, sealed envelopes. Envelopes will be prepared prior to the start of the study by a research assistant not involved in the research. Each participant will be allocated to one of the groups respecting the contents inside the envelopes. To minimize possible bias resulting from participants not being blinded, they will be instructed not to comment to the examiner about the group to which they were assigned.

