#### **Feasibility of the intervention**

The feasibility of the intervention will be determined by examining retention, follow-up of individuals, attendance, safety, and perceived effectiveness.

Retention will be determined by the ratio of the total number of individuals who completed the proposed intervention program to the total number of individuals who began the proposed intervention program. The reasons for dropping out of the intervention program will be recorded (Peniche et al., 2022, Kim et al., 2020, Regan et al., 2021, Hanlon et al., 2022).

The follow-up of individuals will be determined by the ratio between the total number of individuals who remained in the same group to which they were initially allocated until follow-up and the total number of individuals who were allocated (Regan et al., 2021).

Attendance will be determined by the ratio between the total number of sessions held and the total number of sessions offered. The number and reasons for absence from sessions will be recorded (Caetano et al., 2023, Peniche et al., 2022, Regan et al., 2021).

Safety will be determined by the number and reasons for adverse events (e.g., pain, falls, hospitalization, and death) identified during the individual's intervention and follow-up period (Caetano et al., 2023, Regan et al., 2021, Hanlon et al., 2022).

Perceived effectiveness will be determined by the following question: “Comparing how it was before you performed the intervention and now, do you think your ability to perform routine physical activity is: much worse, moderately worse, a little worse, the same, a little better, moderately better or much better?” The answer provided will be recorded by the independent examiner.

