## **2.7 Procedures**

During the execution of the study, measures to prevent the spread of the coronavirus will be observed (COMITÊ PERMANENTE DE ENFRENTAMENTO DO NOVO CORONAVÍRUS DA UFMG, 2020; MINISTÉRIO DA SAÚDE, 2020). Individuals will be scheduled by time to avoid crowds. When scheduling assessments, a screening will be carried out to assess the presence of flu-like symptoms. In the presence of symptoms, the isolation period will be respected, and the individual will be contacted again after the safety period. Evaluators will use disposable surgical masks. Participants will also be asked to wear masks, and if necessary, procedural masks will be provided for

use during the assessment. When necessary, the mask can be removed to carry out the tests. All reusable equipment will be properly sanitized and sterilized. Finally, 70% alcohol gel will be made available for hand hygiene (COMITÊ PERMANENTE DE ENFRENTAMENTO DO NOVO CORONAVÍRUS DA UFMG, 2020; MINISTÉRIO DA SAÚDE, 2020).

Individuals interested in voluntarily participating in this study will be assessed for eligibility according to the criteria described previously. Those who meet the established criteria will be randomly allocated to an experimental group or control group. All data will be collected by the same previously trained evaluator, with the help of a research assistant, who will be blinded regarding the allocation of participants. Another researcher with the assistance of a research assistant will be responsible for administering the intervention and will be blinded to participant data.

This study will be carried out at the NEUROLAB of the Department of Physiotherapy of the EEFFTO (UFMG).

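### The blinded examiner collects satisfaction with the intervention at weeks 12 and 16, an avoidable risk to the blind for the interview-based outcomes, above all at week 16

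*Protocol*

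**What the plan says.** Section 2.1 of the protocol makes a blinded evaluator a feature of the design. Section 2.5 sets assessments at weeks 0, 12 and 16. For the last two it adds to the form an item on satisfaction: "in addition to the addition of an assessment of the participant's satisfaction with the intervention carried out (APPENDIX 3"). On who completes the form it says "This collection will be carried out by a previously trained examiner, blinded to group allocation", and it follows this with "All participants will be instructed not to comment on information about the training received".

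Section 2.3 gives a similar instruction, because participants themselves cannot be blinded: "they will be instructed not to comment to the examiner about the group to which they were assigned". Section 2.7 states "All data will be collected by the same previously trained evaluator, with the help of a research assistant".

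Sections 2.4 and 2.4.2 say that both arms receive the HEARTS programme and that the activity watch is the sole difference between them.

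Section 2.5.1 adds a question on perceived effectiveness with seven fixed answers. Of this it says "The answer provided will be recorded by the independent examiner".

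**The concern.** Within one section, the person who must not learn the allocation is given the task of asking about the intervention, and the participant is told not to talk about it. Since only the watch separates the arms, a single mention of it discloses the group.

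Participants know their allocation, so the examiner's blind is the main protection left for the between-group comparison. The HAP supplies activity level, the number who became active and estimated cardiorespiratory fitness. It is given by interview, as is the SS-QOL, and blood pressure is read by ear on an aneroid device. All of these leave some room for the examiner's expectation to act. They feed the effect sizes of section 2.8 and the secondary objective of estimating parameters for a later trial.

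**Working it through.** No arithmetic applies. The plan states no figure on this point, and its sample of 12 per group does not bear on it. The check sets the sections side by side.

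1. **Who asks, and when.** Section 2.5 puts the satisfaction item on the week 12 and week 16 form and assigns that form to the blinded examiner. This is explicit.
2. **Whether the same person returns.** Section 2.7 says "All data will be collected by the same previously trained evaluator". Whoever hears the week 12 answer also takes the week 16 measurements.
3. **What stands in the way.** The only safeguards stated are the instructions to participants in sections 2.3 and 2.5. No separate collector, self-completed form, order of items or check of the blind is given.
4. **What would disclose allocation.** Both arms receive HEARTS, a diary and weekly calls, so a comment on any of these is neutral. A comment on the watch is not.
5. **Which measurements follow a disclosure.** This depends on where the item sits in the visit:

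| How the satisfaction item is collected | Week 12 clinical measures | Week 16 clinical measures |
|---|---|---|
| By the examiner, before the clinical measures | exposed | exposed |
| By the examiner, after the clinical measures | not exposed | exposed, through what was said at week 12 |
| Self-completed after the clinical measures and sealed | not exposed | not exposed |

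Asking the item last therefore protects week 12 but not week 16.

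6. **Size.** To a first approximation, the bias in a between-group difference is the share of experimental participants who disclose, multiplied by the mean shift in the examiner's ratings once allocation is known. The protocol gives neither quantity, nor anything from which to derive one, so the product cannot be stated.
7. **Which results are touched.** Recruitment, retention, follow-up, attendance and completeness of measurement are ratios of counts and do not rest on the examiner's judgement. The exposed results are the clinical measures of section 2.5.2.

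**The case against.** The strongest reply is that the item itself is in Appendix 3, which is not available here. Section 2.5 speaks only of an assessment of satisfaction. If this is a closed rating, a participant in either arm can answer it without describing what was received, and the instruction not to comment can be kept. The body of the protocol does not define the item further. This objection stands in part. A reader might infer that disclosure is certain because the form forces participants to discuss the watch. The documents do not show that; they show a risk whose size depends on the format.

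A reader might also infer that the perceived-effectiveness question opens the same route. Its wording is given in full in section 2.5.1. It has seven fixed answers about ability to perform routine physical activity, names no device, and can be answered alike in both arms. That its independent examiner is the blinded evaluator is itself an inference from sections 2.5 and 2.7, since section 2.8 uses the same term for the person doing the analysis. This question is not part of the point.

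Three further replies carry some weight:

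- The HAP and SS-QOL use fixed response options, which limits the examiner's discretion.
- Both are self-reports by unblinded participants, and the examiner's blind cannot remove bias from that source.
- Section 2.4.1 has the watch worn throughout waking hours, and nothing says that it is taken off for assessments. If it is visible, it is a more direct route to unblinding. That is a separate matter: closing it would leave this one open, and the reverse.

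None of these replies changes who asks the question, or that the same evaluator returns at week 16.

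**Conclusion.** The point holds as an avoidable risk. The protocol has the blinded examiner collect an assessment of satisfaction with an intervention that participants are told not to discuss, at two visits handled by the same evaluator. If the item draws out a mention of the watch, the examiner is unblinded before the week 16 HAP, SS-QOL and blood pressure measurements, and before those of week 12 if the item comes first.

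This rests on two assumptions: that the format of the item leaves room for such a mention, and that the examiner asks it face to face or reads the answer. The first cannot be checked without Appendix 3.

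A numerical bias should not be attached to this. Any figure would come wholly from assumed rates of disclosure and assumed shifts in rating. Nor does it undermine the primary conclusions of a feasibility study of 24 people: it concerns secondary estimates, already imprecise, that are meant for planning. It is a low-cost improvement that protects a blind on which the design relies.

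**What to change.** Amend sections 2.5 and 2.7 so that the satisfaction item leaves the examiner's form. At weeks 12 and 16 the participant completes it on a separate sheet after all clinical measures are done and seals it in an envelope that the blinded examiner does not open. A companion or caregiver may help, as section 2.4 already allows for the diary. Section 2.7 should then except this sheet from the data that the evaluator collects.

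The perceived-effectiveness question may stay with the examiner, provided that it is asked after the clinical measures, or it may go on the same sheet.

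Collection by telephone through the staff who deliver the intervention should not be used. Section 2.7 keeps those staff blind to participant data. Answers given to the people who delivered the programme would also be open to courtesy bias, and perceived effectiveness is one of the primary feasibility measures.

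The cost is a change of form and wording, with no new staff, visits or participants. The downside is small: a few more satisfaction answers may be missing.

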### **2.5.1 Primary outcomes: feasibility measures**

#### **Recruitment feasibility**

The feasibility of recruitment will be determined by the ratio between the total number of eligible individuals and the total number of individuals screened, and by the ratio between the total number of eligible individuals and the total number of individuals recruited (Caetano et al., 2023, Peniche et al., 2022, Kim et al., 2020, Regan et al., 2021).

#### **Feasibility of the intervention**

The feasibility of the intervention will be determined by examining retention, follow-up of individuals, attendance, safety, and perceived effectiveness.

Retention will be determined by the ratio of the total number of individuals who completed the proposed intervention program to the total number of individuals who began the proposed intervention program. The reasons for dropping out of the intervention program will be recorded (Peniche et al., 2022, Kim et al., 2020, Regan et al., 2021, Hanlon et al., 2022).

The follow-up of individuals will be determined by the ratio between the total number of individuals who remained in the same group to which they were initially allocated until follow-up and the total number of individuals who were allocated (Regan et al., 2021).

Attendance will be determined by the ratio between the total number of sessions held and the total number of sessions offered. The number and reasons for absence from sessions will be recorded (Caetano et al., 2023, Peniche et al., 2022, Regan et al., 2021).

Safety will be determined by the number and reasons for adverse events (e.g., pain, falls, hospitalization, and death) identified during the individual's intervention and follow-up period (Caetano et al., 2023, Regan et al., 2021, Hanlon et al., 2022).

Perceived effectiveness will be determined by the following question: “Comparing how it was before you performed the intervention and now, do you think your ability to perform routine physical activity is: much worse, moderately worse, a little worse, the same, a little better, moderately better or much better?” The answer provided will be recorded by the independent examiner.

### **Feasibility of obtaining clinical measurements**

The feasibility of obtaining clinical measurements will be determined by the percentage of clinical outcomes measured (ratio between the number of clinical outcomes measured and the number of clinical outcomes proposed to be measured) and the percentage of participants who completed the diary (ratio between the number of individuals who completed the diary and the number of individuals who started the proposed intervention program) (Caetano et al., 2023).

#### **2.5.2 Secondary outcomes: clinical measures**

Clinical outcomes will be evaluated to estimate the parameters for carrying out an RCT, including: level of physical activity and number of individuals post-stroke who became physically active, SBP and DBP, cardiorespiratory fitness, self-efficacy for physical activity and health-related quality of life.

The level of physical activity and the number of individuals post-stroke who became physically active will be measured with the HAP (Souza et al., 2006). The HAP is a questionnaire, applied in the form of an interview, consisting of 94 activities, each one graded hierarchically according to the metabolic equivalent required (Teixeira-Salmela et al., 2007, Souza et al., 2006). Activities include personal care, transportation,

home maintenance, social and leisure activities, and physical exercise. For each item, there are three possible answers: “still does the activity”, “stopped doing it” and “never did it” (Teixeira-Salmela et al., 2007, Souza et al., 2006). The maximum activity score (MAS) indicates the activity with the highest energy expenditure that the individual is capable of performing (Teixeira-Salmela et al., 2007, Souza et al., 2006). An AAS is obtained by subtracting from the maximum score the number of activities that the individual stopped performing and indicates the average level of typical metabolic equivalent (Teixeira-Salmela et al., 2007, Souza et al., 2006). Higher scores indicate better results (Souza et al., 2006). The level of physical activity will be operationalized by the AAS, in points (Souza et al., 2006). Another measure of the HAP is the “Activity Classification”, which provides an overall classification of the individual's activity level into “Inactive”, “Moderately active” and “Active”. The number of individuals who have become “Moderately Active” and “Active” will be identified. The HAP is an instrument already adapted to Portuguese-Brazil, which presents appropriate measurement properties for assessing the level of physical activity of individuals post-stroke (Teixeira-Salmela et al., 2007, Souza et al., 2006).

SBP and DBP will be operationalized as the average of the pressures obtained. These measurements will be obtained using the Tycos® aneroid sphygmomanometer (WelchAllyn Inc., NY, USA, Model DS-44) and the stethoscope (Litmann Classic II SE 3M®, USA).

Cardiorespiratory fitness will be measured by HAP (Souza et al., 2006). One of the HAP measures is “Lifestyle Energy Consumption”, operationalized in  $\text{ml.kg}^{-1}.\text{min}^{-1}$  (Souza et al., 2006). The HAP is a valid instrument for estimating the cardiorespiratory fitness of individuals post-stroke (Brito et al., 2022).

Self-efficacy for physical activity will be operationalized considering the score obtained on the Self-Efficacy for Physical Activity Scale (Rech et al., 2011). No instrument was found that presents adequate measurement properties to assess self-efficacy for physical activity in individuals post-stroke. The scale presents 10 questions, divided into two sections (Rech et al., 2011). Each question must be answered as yes (1 point) or no (0 point) (Rech et al., 2011). Scores are computed with the sum of the answers to each question (Rech et al., 2011). The higher the value, the higher the self-efficacy for practicing physical activity (Rech et al., 2011). Rech et al. (2011) investigated the measurement properties of the scale and identified that it presents adequate validity,

internal consistency and reproducibility to assess self-efficacy for physical activity in Brazilian adults.

Health-related quality of life will be operationalized considering the scores obtained on the Stroke-Specific Quality of Life Scale (SS-QOL) (Ciconelli et al., 1999, Lima et al., 2008). The Brazilian version of the SS-QOL has twelve domains (energy, family role, language, mobility, humor, personality, self-care, social role, reasoning, upper limb function, vision and work/productivity), totaling 49 items (Lima et al., 2008). There are three possible answers, on a scale of five to one: amount of help needed to perform specific tasks, amount of difficulty experienced when it is necessary to perform a task and degree of agreement with statements about functionality (Lima et al., 2008). The minimum possible score is 49 (worst perception of health-related quality of life) and the maximum score is 245 (best perception of health-related quality of life) (Lima et al., 2008). The reference for responses is the previous week (Lima et al., 2008). This instrument is applied in the form of an interview, can be administered in a short time and has good clinical applicability and adequate measurement properties for evaluating this outcome in individuals post-stroke (Ciconelli et al., 1999, Lima et al., 2008, Cabral et al., 2012). This instrument has already been translated and adapted into Brazilian Portuguese (Ciconelli et al., 1999, Lima et al., 2008).

## **2.6 Sample calculation**

As a feasibility study, no formal sample size calculation is performed (Billingham et al., 2013). Following the recommendation proposed by Julious (2005) for feasibility studies with parallel groups, the present study will present a sample size of 24 individuals, with 12 individuals in each group.

## **2.7 Procedures**

During the execution of the study, measures to prevent the spread of the coronavirus will be observed (COMITÊ PERMANENTE DE ENFRENTAMENTO DO NOVO CORONAVÍRUS DA UFMG, 2020; MINISTÉRIO DA SAÚDE, 2020). Individuals will be scheduled by time to avoid crowds. When scheduling assessments, a screening will be carried out to assess the presence of flu-like symptoms. In the presence of symptoms, the isolation period will be respected, and the individual will be contacted again after the safety period. Evaluators will use disposable surgical masks. Participants will also be asked to wear masks, and if necessary, procedural masks will be provided for

use during the assessment. When necessary, the mask can be removed to carry out the tests. All reusable equipment will be properly sanitized and sterilized. Finally, 70% alcohol gel will be made available for hand hygiene (COMITÊ PERMANENTE DE ENFRENTAMENTO DO NOVO CORONAVÍRUS DA UFMG, 2020; MINISTÉRIO DA SAÚDE, 2020).

Individuals interested in voluntarily participating in this study will be assessed for eligibility according to the criteria described previously. Those who meet the established criteria will be randomly allocated to an experimental group or control group. All data will be collected by the same previously trained evaluator, with the help of a research assistant, who will be blinded regarding the allocation of participants. Another researcher with the assistance of a research assistant will be responsible for administering the intervention and will be blinded to participant data.

This study will be carried out at the NEUROLAB of the Department of Physiotherapy of the EEFFTO (UFMG).

## **2.8 Statistical Analysis**

All statistical analyzes will be carried out by an independent examiner, blinded to all procedures carried out in the study, including group allocation. Descriptive statistics will be calculated for all results. Effect sizes will be calculated to determine the magnitude of within- and between-group comparisons. All analyzes will be carried out using the SPSS 20.0 statistical program and  $\alpha=0.05$  will be considered, adjusted for multiple comparisons.

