### 2.2 Participants

A convenience sample will be recruited in the community of the city of Belo Horizonte, through contact with outpatient clinics, clinics, hospitals, health centers, associations, research groups and extension projects developed with the population of interest.

To participate in the study, individuals must meet the following inclusion criteria:

- Present a clinical diagnosis of stroke more than six months ago;
- Be 18 years old or over;
- Be classified as “Inactive” according to the Adjusted Activity Score (AAS) of the Human Activity Profile (HAP) (Souza et al., 2006);

- Be able to walk 10 meters independently with or without a walking aid (considering that walking is a potential way to participate in physical activity);
- Present medical clearance to practice physical activity.

The following individuals will be excluded:

- Those who test positive for possible cognitive impairment (Mini-Mental State Examination) using the cutoff point based on educational level (Bertolucci et al., 1994) and/or have comprehension aphasia, assessed by the ability to respond to verbal commands using body movements (“raise your unaffected arm and open your hand”) (Teixeira-Salmela et al., 2007);
- Those with the presence of pain or other adverse health conditions that compromise the implementation of the proposed intervention program, such as vestibular disorders, severe arthritis, or any other diagnosed nervous system disease.

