### **2.4 Intervention**

Participants will undergo an intervention program involving the HEARTS technical package (OPAS, 2019) and the experimental group will have the addition of self-monitored physical activity using the Smartwatch Mi Band 7®. Therefore, the only difference between the groups is that participants in the control group will not receive the physical activity monitor (Smartwatch Mi Band 7®). To monitor adherence to the protocol, individuals will receive a diary of regular physical activity, which will be filled

out, for each day of physical activity, the duration and the subjective effort score according to the Modified Borg Categorical Scale (Borg, 1982, Cavallazzi et al., 2008) (APPENDIX 2). The researcher responsible for implementing the intervention (physiotherapist with previous experience in caring for individuals post-stroke and one of the researchers responsible for the present study) and a research assistant (scientific initiation students from the undergraduate physiotherapy course) will be trained in advance for standardization. implementation of intervention protocols, which will always be carried out by the same therapist. A companion/caregiver will be instructed to assist the individual in filling out the diary, if necessary.

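### Entry and baseline rest on the same low HAP score, so within-group effect sizes for HAP outcomes and the raw count who became active are biased upward in expectation

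*Protocol*

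**What the plan says.** Protocol section 2.2 requires participants to be Inactive on the AAS of the Human Activity Profile (HAP). Section 2.5 sets assessments at weeks 0, 12 and 16, and says of week 0 that "clinical and demographic data will be collected from all individuals for the purpose of verifying the eligibility criteria". No separate screening HAP and no second HAP before randomisation is described, so one administration appears to serve for both selection and baseline.

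Three clinical outcomes in section 2.5.2 come from the same questionnaire:
- "The level of physical activity will be operationalized by the AAS, in points";
- "the number of individuals post-stroke who became physically active will be measured with the HAP", counting those who move to Moderately active or Active;
- "Cardiorespiratory fitness will be measured by HAP", through its energy-consumption estimate.

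That section gives the purpose of the clinical outcomes as estimating parameters for a later randomised trial. Section 2.8 commits to the analysis: "Effect sizes will be calculated to determine the magnitude of within- and between-group comparisons". On the comparison itself, section 2.4 says that "the only difference between the groups is that participants in the control group will not receive the physical activity monitor".

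**The concern.** When people enter because a score is low, and that same score is the baseline, some of them are low by measurement error or a poor week. At retest their scores move back towards their usual level without any treatment effect. The expected within-group change in AAS is then positive for any retest correlation below 1. The activity class behaves the same way: everyone starts as Inactive by the entry rule, so the count who became active starts at zero and can only rise. HAP-based fitness shares the bias to the extent that it correlates with the AAS.

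Section 2.8 nevertheless treats within-group effect size as a measure of magnitude, in a study meant to supply planning parameters. The design adds to the risk. The primary objective in section 1.1 concerns the HEARTS package together with the monitor, but both arms receive HEARTS. No randomised contrast estimates the package, so within-group change is the only figure that could be read as its effect. A later trial planned on that figure would build in a spurious gain.

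**Working it through.** **The plan's own figures.** Section 2.6 states that no formal sample size calculation is made; 12 per group × 2 = 24 agrees with the stated total. The protocol gives no AAS cut-off, SD, reliability or expected change, so there is no planned effect to reproduce.

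**Model.** Let X (week 0) and Y (follow-up) be standard bivariate normal with correlation r and no true change. Entry requires X < c, where a share q of the source population lies below c. Write λ = φ(c)/q, with φ the standard normal density.
- Expected gain in population SDs: (1 − r)λ.
- SD of X among those selected: s = √(1 − cλ − λ²).
- Gain in baseline SDs: (1 − r)λ/s.
- Share leaving Inactive: P(Y ≥ c | X < c).

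**Inputs.** r = 0.8 to 0.9 is an assumption. For q, the only proxies in the document are in the Introduction: one Brazilian study with 77% practising no physical activity, and one with 36% practising it, hence 100 − 36 = 64%. Neither is defined by the HAP. A value of 40% is added as a further assumption.

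**Intermediate values.**
- q = 0.40: c = −0.253, φ(c) = 0.386, λ = 0.966, s = 0.558.
- q = 0.64: c = 0.358, φ(c) = 0.374, λ = 0.585, s = 0.670.
- q = 0.77: c = 0.739, φ(c) = 0.304, λ = 0.394, s = 0.744.

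For example, q = 0.64 and r = 0.8 give 0.2 × 0.585 = 0.117 population SD, and 0.117/0.670 = 0.17 baseline SD.

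| q | r | Gain, population SD | Gain, baseline SD | Share crossing | Of 24 |
|---|---|---|---|---|---|
| 0.40 | 0.8 | 0.193 | 0.35 | 24.8% | 5.9 |
| 0.40 | 0.9 | 0.097 | 0.17 | 17.4% | 4.2 |
| 0.64 | 0.8 | 0.117 | 0.17 | 15.0% | 3.6 |
| 0.64 | 0.9 | 0.058 | 0.09 | 10.5% | 2.5 |
| 0.77 | 0.8 | 0.079 | 0.11 | 10.0% | 2.4 |
| 0.77 | 0.9 | 0.039 | 0.05 | 7.1% | 1.7 |

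**Wider range.** With q from 0.30 to 0.77 and r from 0.70 to 0.95, the gain runs from 0.03 to 0.68 baseline SD and the share crossing from 5% to 37% (1.2 to 8.8 of 24). Simulation of 2,000,000 draws per setting agreed with the formula for the gain.

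**Sampling error.** The SD of change is √((1 − r)²s² + 1 − r²). With 12 people, the standard error of the mean change at q = 0.64 to 0.77 and r = 0.8 to 0.9 is 0.17 to 0.27 baseline SD. That exceeds the bias at the same settings.

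**Between arms.** Both arms are selected by the same rule, so the expected difference in change is zero. Simulated at q = 0.64, r = 0.9 and 12 per arm, the mean difference was 0.000, against a mean within-arm gain of 0.058 population SD.

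**The case against.** The strongest reply is that little hangs on this. The study's purpose is feasibility, and recruitment, retention, follow-up, attendance, safety and completeness of measurement do not depend on change in the AAS. The between-group comparison is already planned and is unbiased. The protocol nowhere says that within-group change is the effect of the package or will size the later trial, and it does not rule out reporting the count by arm. All of this stands, and it limits the weight of the point. It does not remove it, because section 2.8 names within-group effect size as a magnitude and section 2.5.2 ties the clinical outcomes to planning.

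A reader might go further in four ways that the documents do not support.
- That the groups *will* show improvement from this cause. This is true in expectation only; in a sample of 12, chance can outweigh it.
- That the bias is large. The 40% figure is an assumption, and the protocol's own proxies give smaller values, though these are not HAP-defined either.
- That all within-group effect sizes should be deleted. Blood pressure, self-efficacy and SS-QOL are not selected on.
- That the absence of a stated baseline covariate is itself an error. Such model detail is commonly left to an analysis plan, which is not shown here, and it affects precision rather than this bias.

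**Conclusion.** The point holds for the HAP-derived secondary outcomes. Following the plan as written gives within-group effect sizes for the AAS and, by correlation, HAP-based fitness that are biased upward in expectation, together with a raw count of people who became active that would be above zero in expectation under a programme with no effect.

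The direction follows from the protocol, given that one week-0 HAP serves for entry and baseline, which is how section 2.5 reads. The size does not. It rests on a normal model, an assumed retest correlation of 0.8 to 0.9 and an unknown share of HAP-inactive people: about 0.05 to 0.17 baseline SD and 2 to 4 of 24 at the 64% and 77% proxies, or 0.17 to 0.35 SD and 4 to 6 of 24 at 40%. The randomised contrast is sound, and the primary feasibility conclusions are not called into question. This is a correction worth making before results are used for planning, and not a flaw in the trial as a whole.

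**What to change.** In section 2.8:
1. Present within-group change in HAP outcomes as descriptive only, with means and SDs by arm and visit, and not as a magnitude of effect.
2. Take the effect parameters for the later trial from the between-arm difference at weeks 12 and 16, adjusted for the week-0 value, with a 95% CI. The adjustment is there for precision.
3. Report the number who became active by arm, with the between-arm difference and its CI.

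In section 2.8 or 1.1, state that this contrast estimates the addition of the monitor to HEARTS and not the effect of the whole package.

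The cost is a few sentences and one degree of freedom per model. No new data or visits are needed.
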